## Abstract

**Background:**

Many stress-related mental health problems, like depression and anxiety, emerge during adolescence, with some recent studies suggesting numbers are increasing. One possible way to reduce adolescents' vulnerability to stress-related mental health problems is to increase their resilience by training them in recalling specific positive memories and anticipating specific positive future events. Therefore, an innovative *combi*-training (called Positive Events Training; PET) was developed, focusing on the enhancement of the specificity of *both* past and future positive autobiographical events in adolescents. Its effects on adolescents' resilience and mental wellbeing will be examined.

**Methods:**

A cluster randomized controlled trial with a 2 (condition) × 3 (time-point) factorial design was conducted. Classes of adolescents were randomized to either a PET program (intervention) or a CREAtive writing Training (CREAT) program (active control). Both trainings consisted of four sessions of 50 min (one session, weekly, for four consecutive weeks) and were delivered in schools. Before (pre-training, T1), immediately after (post-training, T2), and 2 months after the training (follow-up, T3), participants completed a series of self-report questionnaires. Primary outcomes are resilience and mental wellbeing. Secondary outcomes are positive affect, positive affect regulation and anhedonia. CONSORT criteria for conducting and reporting RCTs will be used.

**Ethics and dissemination:**

Ethical approval was obtained from the Social and Societal Ethics Committee (SMEC) and the study has been preregistered on Open Science Framework (OSF) and ClinicalTrials.gov (Trial registration number: NCT05757180). We plan to develop a free, online, web-based self-directed PET protocol for teachers if the study provides evidence for the effectiveness of the PET program in increasing adolescents' resilience and mental wellbeing, so teachers can deliver the program to future students without the need of professional external trainers.

## 1 Introduction

### 1.1 Rationale

Many stress-related mental health problems emerge during adolescence and represent the largest cause of the burden of disease among young people (1). Furthermore, there has been a significant increase in the prevalence of anxiety between 2012 and 2018 (2) and of depression symptoms over the past 20 years (3) in adolescents. Such problems have a profound and often lasting impact on young people's future (1).

One important way to reduce the burden of disease due to stress-related mental disorders is to shift the focus from addressing deficits to strengthening protective factors. This fits with the call to complement a treatment approach with a preventative approach (4). Our study adopts such a preventative approach, examining ways to strengthen adaptive and protective factors. An important protective factor in this context is resilience, which is the capacity to bounce back from stressful life events. It is associated with better mental wellbeing (5), and with higher quality of life in adolescents (6). Strengthening factors related to resilience can, thus, be expected to improve mental wellbeing.

Recent basic research indicates that recalling specific positive memories is one such resilience-enhancing factor, both in adults and adolescents. Studies show that recalling specific positive memories is associated with reduced vulnerability to emotional problems in the face of stress (7), actively buffers the physiological and emotional consequences of stress (8), repairs negative mood (9, 10), and is associated with improvement in problem solving and hopelessness (11). The recall of specific positive memories attenuates negative self-cognitions and dampens cortisol responses after exposure to stress (7, 8). These findings align with pilot studies showing that recalling specific positive memories has positive effects on resilience and mental wellbeing. For example, positive MEmory Specificity Training (MEST) has been found to facilitate letting go of negative self-thoughts in adolescents compared to a control training (12).

In a similar vein, research suggests that anticipating specific future positive events holds promise as a potential focus for resilience and mental wellbeing promoting interventions. Basic research in young adults shows, for example, that anticipating positive events leads to improved coping and recovery following stress (13). Such findings align with results from an initial intervention study and clinical trial in depression showing that Future Event Specificity Training (FEST) in adults leads to increased anticipated and anticipatory pleasure for future events and a stronger perception that one has control over future events, which are essential ingredients to mitigate the negative influence of stressful events (14, 15).

So far, studies have focused either on increasing specificity of memories *or* future events, while it has become clear that both have unique, yet complimentary benefits. Whereas (positive) memory specificity has been linked to less negative thinking (7, 12), improved problem-solving (16, 17), positive self-esteem (18) and reduced depressive symptomatology (19), positive future specificity has been linked to less impulsive behavior in adolescents (20, 21) and emotional states that motivate us to engage in rewarding, more meaningful behaviors that maintain good mental health (15, 22–24). Therefore, we will test for the first time the effects of an innovative *combi*-training (called Positive Events Training; PET), focusing on the enhancement of the specificity of *both* past and future positive events in adolescents. Studies showed that there is considerable overlap in the brain structures that are involved in thinking of past and future events. A recent meta-analysis showed that both processes of past and future thinking have cerebral bases that involve the medial temporal lobe (including the hippocampus), as well as frontal, temporal, and parietal areas (25). Interestingly, however, some of these regions were consistently more strongly engaged during future thinking than remembering, suggesting that the former involves additional constructive processes (26). The added value of working with memories and future events is that it will allow people to integrate past, present, and future experiences, which is important for creating a sense of meaning, purpose, and direction in one's life, which contributes to mental wellbeing.

There appear to be many candidate mechanisms by which the representation of specific positive events is believed to promote resilience and wellbeing (7, 27). However, one key mechanism, both for past and future positive events, is thought to be positive emotions. Research shows that the ability to increase positive emotions plays an essential role in resilience (8, 13). One of the key reasons why resilient individuals are able to bounce back more effectively from stressful experiences is that they use positive emotions when dealing with stress (28). Positive emotions buffer against stress and strengthen people's coping repertoire (29). Importantly, such emotions can be induced via the recollection and anticipation of positive events (8, 13, 14, 23).

### 1.2 Hypotheses

The first and main aim is to examine the effects of the PET program on resilience and mental wellbeing as primary outcomes. It is expected that PET will cause an increase in resilience and mental wellbeing at post-intervention and at follow-up. The second aim is to examine the effects of the PET program on secondary outcomes related to positive emotions, as positive emotions are believed to be a central way via which the PET program leads to increased resilience and better mental wellbeing. In particular, we focus on (i) the present moment experience of positive emotions, (ii) the regulation of positive emotions when they are experienced, and (iii) the basic capacity to experience pleasure (or the lack of that capacity, called anhedonia).

So besides looking at the experience of positive emotions as such, we will also explore the impact of the PET program on how adolescents regulate such positive emotions. This is an important focus, as research shows that regulation of positive emotions is also a prominent factor in the development or prevention of emotional problems. For example, youngsters who typically dampen or downplay positive emotions (by using thoughts such as “These good feelings won't last”) are more likely to suffer mental ill-health (30, 31). On the contrary, youngsters who deploy more of a savoring response (e.g., “I'm attempting to fully feel and enjoy this positive emotion”) are typically better off when it comes to mental wellbeing, as savoring responses amplify and extend positive emotions (30, 31).

In the context of positive emotion and its regulation, we will also examine the impact of the PET program on anhedonia. In contrast to dampening or savoring, anhedonia refers to a lack of capacity to experience interest or pleasure in activities that might otherwise be thought to be rewarding (32). In addition, it refers to the diminished pleasure from anticipation to future positive events and to the decreased motivation to pursue positive outcomes. The reduced perception of reward or pleasure in young people has been linked to diverse negative outcomes, reflecting varying degrees of mental ill-health (33–36). Fortunately, the ability to imagine positive future events, which is targeted in the PET program, is associated with both the anticipation and present-moment experience of pleasure (37). So, examination of the effects of the PET program on anhedonia will help to establish whether the training affects not only the experience of positive emotion and regulatory processes, but also the underlying capacity to experience them. Furthermore, according to Hallford et al. (15), reducing anhedonia can promote mental wellbeing. Future Event Specificity Training (FEST) seems to be an intervention that can lead to less anhedonia and an increase in anticipatory and anticipated pleasure. At 3 months follow-up, other clinical and mental wellbeing outcomes were also found (e.g., less likelihood of reaching threshold for a depressive episode, increased behavioral activation, improved global functioning) (15).

## 2 Materials and methods

### 2.1 Study design and sample size

A cluster randomized controlled trial with a 2 (condition; PET program vs. CREAT program) × 3 (time point; baseline, post-training, and follow-up) factorial design was conducted. Classes of adolescents were asked to complete measures of the study outcomes at all three time points (see procedure).

A total sample of 130 adolescents (i.e., *N* = 65 for each condition) provides 80% statistical power to investigate the effectiveness of the PET program, with an alpha of 0.05 and estimated medium effect sizes of 0.25 (38). Given previous (large) effect sizes ranging from *d* = 0.82 (for increased specificity) to *d* = 1.78 (for anticipated pleasure) (11, 14), this more conservative effect size estimate will help mitigate against Type II errors. However, in anticipation of considerable drop-out rates, some oversampling was done. We intended to recruit 15% extra participants (based on drop out of ±17% in previous school study of our lab), resulting in an sample size of approximately 150 participants (75 per group).

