### 2.5 Outcomes

Primary outcomes are resilience and mental wellbeing. Secondary outcomes are positive affect, positive affect regulation and anhedonia.

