### 2.8 Statistical analysis plan

All analyses will be completed in accordance with CONSORT standards. Intent-to-treat analysis will be used. Our primary and secondary outcomes will be analyzed using analysis of variance (mixed ANOVA) with time (pre, post, 2-month follow-up) as a within-subjects factor, and condition (PET, CREAT) as a between-subjects factor. Any baseline differences will be covaried in analyses.

To take into account the repeated measure nature of the study, group differences for the continuous variables at post-training and at follow-up will be tested via a mixed ANOVA model. A model with a main effect for time and for group (PET program vs. CREAT program), random effects for the dummy variables representing time clustered within individuals, and an interaction between time and group will be run to detect changes between groups for the primary and secondary outcomes. Follow-up independent samples *t-*tests will be calculated to examine group differences at post-training and follow-up time points. To correct for the inflated risk of a Type I error from multiple comparisons, Benjamini and Hochberg's (65) false discovery rate procedure will be applied to the main outcomes (i.e., primary and secondary outcomes). Although sample size planning was based on mixed ANOVA modeling, multilevel analyses that take into account the dependence in the data at school-level (clusters) will also be conducted to account for possible variance due to school membership.

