### 3.2 Dissemination plan

We plan to share consolidated findings in an article, which will be submitted for publication in a peer-reviewed journal. Furthermore, we plan to develop a free, online, web-based self-directed PET protocol for teachers if the study provides evidence that the PET program is effective in increasing adolescents' resilience and mental wellbeing, so teachers can deliver the program to future students without the need of professional external trainers.

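### The 80% power in section 2.1 is for one outcome at an uncorrected alpha of 0.05, not for the Benjamini-Hochberg rule by which section 2.8 judges the primary outcomes

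*Protocol article*

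**What the plan says.** Section 2.1 states the planned size and its power: 65 adolescents per condition, 130 in all, which "provides 80% statistical power to investigate the effectiveness of the PET program, with an alpha of 0.05 and estimated medium effect sizes of 0.25". The sentence does not mention several outcomes or a corrected alpha. The only allowance added is for drop-out ("We intended to recruit 15% extra participants"), giving about 150.

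Section 2.5 lists five outcomes: "Primary outcomes are resilience and mental wellbeing. Secondary outcomes are positive affect, positive affect regulation and anhedonia". Section 2.8 sets the multiplicity rule: the Benjamini-Hochberg "false discovery rate procedure will be applied to the main outcomes (i.e., primary and secondary outcomes"). It names a mixed ANOVA with a time-by-group interaction as the main model, adds independent-samples t-tests at post-training and follow-up, and says that the sample size was planned on the mixed ANOVA. Section 2.2 reports that 188 adolescents took part (95 and 93).

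**The concern.** The article gives both a power figure and a decision rule, and the two use different significance thresholds. Under Benjamini-Hochberg with five tests, the p-value that a primary outcome must reach lies between 0.01 and 0.05, depending on how many of the other outcomes are also rejected. An adjusted p-value is never smaller than the raw one, so power under the correction cannot exceed that of the uncorrected test and falls short whenever the correction bites.

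What is at stake is how a null result is read. Section 2.1 presents its effect-size choice as protection against Type II error. A primary outcome that misses significance after correction would be taken as the result of an 80%-powered test when, for that same test, the power was lower.

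**Working it through.** **Inputs.** From section 2.1: n = 65 per arm, alpha 0.05, effect size 0.25, planning drop-out about 17%. From 2.5: two primary and three secondary outcomes. From 2.2: 188 enrolled. Assumed, because the article does not state them: 0.25 is Cohen's f (so d = 2f = 0.5 for two equal groups), tests are two-sided, pupils are independent, and the outcomes share a common correlation of 0 to 0.7.

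**Step 1: reproduce the 80%.** For a two-sample t-test, the noncentrality is d·√(n/2) = 0.5·√32.5 = 2.85 on 2·65 − 2 = 128 degrees of freedom. Power at two-sided alpha 0.05 is 0.808, and 80% needs 64 per arm (128 in total). Other readings do not return 130: d = 0.25 gives power 0.29, a one-sided test at d = 0.5 gives 0.88, and a repeated-measures between-group F with three measures needs 86 at a within-person correlation of 0.5, or 104 at 0.7. The stated figure therefore matches one between-group test of one outcome without correction.

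**Step 2: the thresholds under the 2.8 rule.** With m = 5, the step-up thresholds are 0.05·k/5, that is 0.01, 0.02, 0.03, 0.04 and 0.05. At 65 per arm and d = 0.5, the t-test has power 0.594 at 0.01, 0.689 at 0.02 and 0.808 at 0.05.

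**Step 3: power for one primary outcome under the full procedure.** Simulated t statistics for five outcomes, Benjamini-Hochberg at 0.05. Drop-out of 17% leaves 188 × 0.83 = 156, or 78 per arm.

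| Outcomes that respond | 65 per arm | 78 per arm |
|---|---|---|
| That primary only (d = 0.5) | about 0.60 | about 0.70 |
| Both primaries only (d = 0.5) | 0.66-0.67 | 0.75-0.77 |
| Primaries d = 0.5, secondaries d = 0.25 | 0.66-0.71 | 0.76-0.80 |
| All five (d = 0.5) | 0.75-0.78 | 0.84-0.86 |
| No correction, for comparison | 0.81 | 0.87 |

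With no drop-out (94 per arm) the corrected range is about 0.80-0.92.

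**Step 4: family size.** The article does not fix the number of tests. It is six if the dampening and savoring parts of the positive-affect-regulation scale are scored separately, and ten if five outcomes are tested at two time points. With ten tests at 65 per arm, power for one primary outcome is about 0.51 if one test has a real effect, 0.56 if two do, and 0.75-0.78 if all ten do.

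**Step 5: the choice of test.** For the time-by-group interaction at N = 130, with a group difference of d = 0.5 at both later time points and none at baseline, power depends on the within-person correlation. Over assumed values of 0.3 to 0.8 it runs from about 0.70 to above 0.99 at alpha 0.05, and from about 0.46 to 0.99 at alpha 0.01.

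**The case against.** The strongest reply is that the planned main analysis is the mixed ANOVA, with the t-tests only as follow-up, so the 0.60-0.78 range is not the power of the main test. This stands. Step 5 shows that the interaction test can have more or less power than the t-test, depending on a correlation that the article does not give. The restated power must therefore name its test. The reply does not rescue the 80%, which reproduces only as a single uncorrected two-group comparison.

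A second reply is that section 1.2 expects effects across the outcomes, so the mild end of the table applies: 0.75-0.78 against a stated 80%. This also stands. The 0.60 case requires the other four outcomes to show no effect. A third is that the 188 enrolled offset much of the loss, which is true before clustering is considered.

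Two stronger readings are tempting and should not be adopted. One is that the plan never carries out the test behind the 80%. It does: section 2.8 plans independent-samples t-tests, and only the threshold differs. The other is that the trial needs both primary outcomes to be significant, because section 3.2 plans a teacher version "if the study provides evidence that the PET program is effective in increasing adolescents' resilience and mental wellbeing". That is dissemination text. Neither the hypotheses nor the analysis section sets a both-must-pass criterion, so joint power is optional information and not a test of the stated 80%.

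**Conclusion.** The point holds as a mismatch between two statements in the article. The arithmetic behind the 80% is sound for what it describes, but it does not describe the rule in section 2.8. For a given test the direction of the error needs no assumption about how many outcomes respond or how they correlate. Its size does: at N = 130 the two-group test loses about 20 points if a single outcome responds, and ends only about 2-5 points below the stated 80% if all five respond at d = 0.5. At about 78 per arm, corrected power for one primary outcome is roughly 0.70-0.86, so achieved enrolment largely offsets the loss.

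These figures rest on f = 0.25, two-sided tests, five outcomes in the family and independent pupils. Clustering by class is a separate matter and is not included.

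**What to change.** In section 2.1, state that the 80% applies to one outcome at an uncorrected alpha of 0.05. Then add the power for each primary outcome under the Benjamini-Hochberg rule of section 2.8, at both N = 130 and the achieved sample. Name the assumptions behind it:

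- the test (t-test or mixed-ANOVA interaction);
- the within-person correlation, where the interaction is used;
- the number of tests in the Benjamini-Hochberg family;
- the number of outcomes assumed to respond, and by how much.

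Say also whether the figure allows for clustering. The power to reject both primaries may be added as information only.

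The cost is one reworded paragraph and a short simulation, and a power statement that looks somewhat less favourable. No further participants or data are needed, and the analysis stays as planned.

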### 2.2 Participants

Participants were recruited via secondary schools in Flanders, Belgium. Years 1 to 4 (1st and 2nd grade) of general secondary education were invited to participate, referring to ages 12 – 16. Five different schools (spread across three provinces) participated in the study. Each school selected one pair of parallel classes, which resulted in five pairs of classes (two of the first year, one of the second year, and two of the third year). In total, 188 adolescents participated in the study. Of all the adolescents, 95 were in the PET program (*M*_age_ = 13.2, SD_age_ = 1.00) and 93 in the CREAT program (*M*_age_ = 13.3, SD_age_ = 1.08). Gender distribution was approximately the same in both groups (PET program: 73.6% females, 25.3% males, 2.1% other; CREAT program: 76.3% females, 22.6% males, 1.1% other).

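### The 80% power stated for 130 adolescents is a pupil-level figure; with ten randomised classes it is not supported without qualification

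*Protocol article*

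**What the plan says.** The abstract of the protocol article gives the unit of randomisation: "Classes of adolescents were randomized to either a PET program (intervention) or a CREAtive writing Training (CREAT) program (active control". Section 2.2 reports that each of five schools chose one pair of parallel classes, "which resulted in five pairs of classes", and that 188 pupils took part (95 PET, 93 CREAT).

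Section 2.1 says that 130 adolescents, 65 per arm, "provides 80% statistical power to investigate the effectiveness of the PET program, with an alpha of 0.05 and estimated medium effect sizes of 0.25". It gives no intraclass correlation, design effect or number of classes, and it does not name the metric of 0.25. The value is called conservative by comparison with earlier results: "Given previous (large) effect sizes ranging from *d* = 0.82 (for increased specificity) to *d* = 1.78 (for anticipated pleasure". On attrition the section says "We intended to recruit 15% extra participants (based on drop out of ±17% in previous school study of our lab". The recruitment target it derives from this is about 150, or 75 per arm.

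Section 2.8 begins its last sentence with "Although sample size planning was based on mixed ANOVA modeling" and then announces additional multilevel analyses for dependence at school level.

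**The concern.** Pupils in one class share a trainer group, a timetable and each other, so their outcomes may be correlated. In a class-randomised trial the precision of the group difference depends on the number of classes and the class-level ICC as well as on the number of pupils. A power figure that counts pupils only is therefore an upper bound for the same comparison, and it is reached only if there is no clustering and no cost for having few clusters.

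The article does not leave power to another document. It states 80% outright, in the section that introduces the cluster design. If the trial finds no effect, readers will take that as the result of a trial with 80% power at the stated effect size, and the design as described does not establish this.

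**Working it through.** **Inputs from the article.** N = 130 (65 per arm), alpha 0.05, effect size 0.25 without a metric, 15% oversampling, about 17% drop-out (Section 2.1); ten classes, 188 enrolled (Section 2.2); three time points (Section 2.1).

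**Assumptions, not in the article.** Two-sided test; class ICC 0.01 to 0.10; equal class sizes; where stated, a pre-post correlation of r = 0.6.

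**Step 1: reproduce 130.**
- Two independent groups, f = 0.25, so d = 2f = 0.5. The exact noncentral t gives N = 128 for 80%; at N = 130 power is 80.8%.
- Group-by-time interaction, two time points, noncentrality f² × (N − 2) × (times − 1) = 0.0625 × 128 = 8.0 on 1 and 128 df. At N = 130 power is 80.2%, and 130 is the smallest N that reaches 80%.
- Forms that do not match: d = 0.25 needs 252 per arm; a three-time between-group factor with within-person correlation 0.5 needs 86 in total; a three-time interaction needs 28 or 82, depending on how the noncentrality is defined.

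Both matching forms treat the 130 pupils as independent.

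**Step 2: allow for ten classes.** Let m = N/10 and DE = 1 + (m − 1) × ICC. In SD units the standard error of the group difference is √(4 × DE × (1 − r²)/N), with r = 0 for a comparison at one time point that ignores baseline. The noncentrality is 0.5 divided by this standard error. Three reference distributions are used: normal (design effect only); t on 8 df (ten classes, two arms); and t on 4 df (five pairs, with the conservative assumption that pairing removes no between-class variance).

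Example, N = 130, ICC 0.05: DE = 1 + 12 × 0.05 = 1.60; SE = √(4 × 1.60/130) = 0.222; noncentrality = 2.25. Against critical values of 1.96, 2.306 and 2.776, power is 61.5, 50.9 and 40.6%.

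Power (%) at d = 0.5:

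| Evaluable pupils, model | Reference | ICC 0.01 | 0.02 | 0.05 | 0.10 |
|---|---|---|---|---|---|
| 130, r = 0 | normal | 76.8 | 72.6 | 61.5 | 48.5 |
| 130, r = 0 | 8 df | 65.7 | 61.3 | 50.9 | 39.5 |
| 130, r = 0 | 4 df | 53.3 | 49.5 | 40.6 | 31.5 |
| 156, r = 0 | normal | 83.1 | 78.4 | 66.1 | 51.2 |
| 156, r = 0 | 8 df | 72.5 | 67.4 | 55.0 | 41.8 |
| 156, r = 0 | 4 df | 59.6 | 54.9 | 44.1 | 33.4 |
| 156, r = 0.6 | 8 df | 89.0 | 85.1 | 73.9 | 58.9 |
| 156, r = 0.6 | 4 df | 77.7 | 73.0 | 61.0 | 47.4 |

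The 156 is 188 × 0.83. For 130 pupils without baseline adjustment, the normal approximation falls below 80% once the ICC exceeds about 0.003. On 8 df power is already 70.5% at an ICC of zero, and on 4 df 57.8%.

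**Step 3: drop-out.** 130 × 1.15 = 149.5, which gives the stated 150. After 17% loss, 150 × 0.83 = 124.5 remain, below 130, and pupil-level power is 79.0%. Covering 17% needs 130/0.83 = 156.6, so 157. The 188 enrolled leave 156 after the same loss, so this part has been overtaken.

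**The case against.** The strongest reply is that the table's most pessimistic rows are pessimistic by construction. Section 2.8 plans a three-time model that includes baseline, so a comparison at one time point understates precision. The 4 df rows pay for pairing in degrees of freedom and gain nothing from it. If pairing removed half the ICC (assumed), the 130-pupil 4 df row would be about 56, 54, 48 and 42%; with r = 0.6 and 156 pupils it would be about 80, 78, 72 and 62%. The article does not say outright that allocation was made within school pairs, so the choice between 8 and 4 df is itself an assumption. All of this stands. It is why a range is shown and no single corrected power is offered.

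It can also be said that Section 2.8 tells the reader that planning was based on mixed ANOVA and that multilevel analyses will follow. That discloses the basis, but it does not qualify the 80% in Section 2.1. The added analysis is also described at school level, whereas classes were randomised.

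Three stronger readings are tempting and are not supported:
- **The trial is underpowered by a known amount, or could detect only a considerably larger effect than d = 0.5.** The article gives neither an ICC nor a pre-post correlation. With r = 0.6, 156 pupils and 8 df, power exceeds 80% at ICC 0.01 and 0.02.
- **The 130 must come from a simple two-group test.** The two-time interaction fits at least as well and agrees better with Section 2.8. The article never writes d = 0.5; that is inferred from f = 0.25.
- **The 0.25 is a d, so power is 29%.** The neighbouring d values invite this, but 0.25 is called medium and only f = 0.25 reproduces 130. As d = 0.5 it is indeed smaller than 0.82. Section 2.1 already names the outcomes behind the cited values. What is missing is a label.

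**Conclusion.** The point holds as a defect in a stated property of the design. The 80% for 130 adolescents reproduces under formulas that treat pupils as independent, while ten classes were randomised. For the same comparison at d = 0.5, the design effect alone takes power to between about 77% (ICC 0.01) and 48% (ICC 0.10), and cluster-level degrees of freedom take it lower. With 156 evaluable pupils the detectable d at 80% power runs from about 0.44 (8 df, r = 0.6, ICC 0.01) to about 0.95 (4 df, r = 0, ICC 0.10). That span rests on assumed values of the ICC, the baseline correlation and the benefit of pairing. It shows that the 80% cannot be stated without qualification; it does not show what power the trial had.

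The drop-out slip is correct arithmetic but minor: seven pupils, and pupil-level power of 79.0% where 130 pupils would give 80.8%.

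**What to change.** Change the text only, in Section 2.1 and wherever the power statement is repeated in the results paper:
- Withdraw the unqualified 80%, or say that it is a pupil-level figure that ignores clustering by class.
- Restate power, or the minimum detectable effect, for the ten enrolled classes over a range of class-level ICC. Use cluster-level degrees of freedom, and state the assumed baseline correlation and the treatment of pairing.
- Label 0.25 as Cohen's f, equivalent to d = 0.5 for two equal groups.
- Note that covering 17% drop-out from 130 would have needed 157 recruits rather than about 150, and that the 188 enrolled exceed this.

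Data collection is complete (Section 2.10), and no extra enrolment is proposed. The cost is a short rewrite and a stated power that is less favourable than the present one.
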